## Abstract

**Background:**

Fractures of the long bones and femur fractures in particular are common in multiple trauma patients, but the optimal management of femur fractures in these patients is not yet resolved. Although there is a trend towards the concept of "Damage Control Orthopedics" (DCO) in the management of multiple trauma patients with long bone fractures as reflected by a significant increase in primary external fixation of femur fractures, current literature is insufficient. Thus, in the era of "evidence-based medicine", there is the need for a more specific, clarifying trial.

**Methods/Design:**

The trial is designed as a randomized controlled open-label multicenter study. Multiple trauma patients with femur shaft fractures and a calculated probability of death between 20 and 60% will be randomized to either temporary fracture fixation with fixateur externe and defined secondary definitive treatment (DCO) or primary reamed nailing (early total care). The primary objective is to reduce the extent of organ failure as measured by the maximum sepsis-related organ failure assessment (SOFA) score.

**Discussion:**

The Damage Control Study is the first to evaluate the risk adapted damage control orthopedic surgery concept of femur shaft fractures in multiple trauma patients in a randomized controlled design. The trial investigates the differences in clinical outcome of two currently accepted different ways of treating multiple trauma patients with femoral shaft fractures. This study will help to answer the question whether the "early total care" or the „damage control” concept is associated with better outcome.

**Trial registration:**

Current Controlled Trials ISRCTN10321620

## Background

Trauma is a major medical and economical issue of health care systems today and the leading cause of death between the age of 1 and 45 years [1]. The World Health Organization assumes that death caused by accidents, violence and war will even increase until 2020. The implications for the society are serious, as most of the trauma victims are young and at the beginning of their careers [2,3].

Fractures of the long bones and femur fractures in particular are common in multiple trauma patients, but the optimal management of femur fractures in these patients is not yet resolved [4,5]. In principle, there are five methods for the treatment of these fractures: cast, extension, external fracture fixation with fixateur externe, and internal fixation with either intramedullary nail or plate osteosynthesis.

Of the five possibilities of treating femoral fractures, cast or extension therapy was considered standard therapy for long bone fractures in multiply injured patients in the 1960s, but this strategy gradually became obsolete. Observational studies showed that mortality rates were reduced by initial fracture stabilization, independent of the procedure performed (fixateur externe, nail or plate). This led to a new standard therapeutic concept for long bone fracture treatment in multiple trauma patients from the mid 1980s on, termed "early total care" [4,5].

But, the question remained whether primary internal (nail/plate) or external fixation (fixateur externe) is advantageous for this patient population, especially in high risk patients with additional chest or head injuries [4,5]. While nailing (in contrast to plate osteosynthesis) is considered the gold standard for treatment of isolated femur shaft fractures because of its undeniable advantage of weight-bearing structure, it is compromised by the significant distress caused by operation time, blood loss, and insertion of the nail, which may act as a "second hit". Studies comparing reamed and unreamed intramedullary nails show the superiority of the reamed nail [6,7].

On the other hand, advocates of temporary external fixation in multiple trauma patients assert its simplicity with regard to initial treatment, as well as hypothetic advantages regarding patient security with less blood loss and possible reduction in systemic response as well as mortality in specific subgroups of trauma patients, e.g. with additional chest or head injuries. However, hypothetic disadvantages of temporary external fixation must also be considered: planned additional surgery for the secondary definitive procedure with prolonged mechanical ventilation and intensive care unit (ICU) stay, planned additional burden for the patient at secondary surgery, increased infection rates by conversion of external to internal fixation, a certain number of patients in which a conversion will not be possible resulting in impaired functional results, moreover the planned conversion within the first days after trauma may also act as a "second hit" to the patient. The optimal time for conversion from external fixation to a definitive procedure is not clear in patients treated with temporary external fixation and secondary intramedullary nailing [8,9].

With respect to the question of "early total care" or temporary fracture fixation by fixateur externe in *all *multiple trauma patients regardless of their anatomic or physiologic injury severity the literature presents a diversity of studies supporting different views. Both a recently published evidence based guideline [4] as well as a current systematic literature review [5] could neither clarify the optimal time point nor procedure of femoral fracture fixation in multiple trauma patients. In addition, an analysis of the German Trauma Registry including more than 8000 multiple trauma patients showed that management differs widely and depends on both the individual hospital strategy as well as on patient/trauma characteristics [5].

In this respect increasing literature evidence suggests that neither "early total care" nor temporary external fixation with secondary definitive internal osteosynthesis should be considered as standard therapy in *all *patients. Instead, decision making should be dependent on the patient's individual risk by its anatomic, physiologic and immunologic injury severity (risk adapted damage control concept): patients with a low mortality risk can be treated by primary definitive fracture fixation while patients at a higher mortality risk should be treated by damage control in the sense of temporary fracture fixation with a fixateur externe and later secondary definitive treatment when the patients' physiologic and immunological situation has been stabilized on the ICU.

Criteria, which have been recommended by various authors in order to define patients, in whom early definitive osteosynthesis might be disadvantageous are named in table 1[10-20]. Unfortunately, up to date, there is no proof for the superiority of the risk adapted damage control concept with regard to evidence based randomized controlled trials nor are the criteria listed in table 1 validated.

**Table 1 T1:** Criteria, which have been recommended by various authors in order to define patients in whom early definitive osteosynthesis might be disadvantageous: Variables not validated.

**Author (year)^[Reference]^**	**Suggested dependent variable**
Trentz (1978) [10]	Cardiopulmonary, coagulation and metabolic criteria

Sturm (1984) [11]	Thoracic trauma

Seibel (1985) [12]	Oxygen transport, coagulation

Burchardi (1990) [13]	Circulation, coagulation

Van Os (1994) [14]	Cardiovascular condition

Reynolds (1995) [15]	Resuscitation, additional injuries (head, chest, pelvic fracture), delay

Friedl (1996) [16]	ISS

Scalea (2000) [17]	Physiology, additional injuries (head, thorax, abdomen)

Rixen (2001) [24]	Prognostic factors: Age, ISS, GCS, BE, coagulation

Pape (2001) [18]	ISS, additional injuries (thorax, abdomen, pelvis), cardiopulmonary criteria, coagulation, temperature, IL-6, „borderline patients“

Kutscha-Lissberg (2001) [19]	Circulation, volume loss, coagulation

Brundage (2002) [20]	Hemodynamics, preoperative resuscitation

**ISS**: Injury Severity Score; **GCS**: Glasgow Coma Scale; **BE**: Base Excess; **IL-6**: Interleukin 6

Thus, both the evidence-based guideline of the EAST organization [4] as well as a systematic literature analysis [5] concluded that a randomized trial is urgently needed to clarify the question whether primary internal fixation (early total care) or temporary external fixation with internal fixation in a second step (in the sense of risk adapted damage control) should be performed in patients with multiple trauma [4,5].

This trial investigates the differences in clinical outcome of primary internal fixation (early total care) or temporary external fixation (damage control) in multiple trauma patients with femoral shaft fractures. The two procedures will be examined concerning the severity of organ failure [sepsis-related organ failure assessment- (SOFA) score as primary endpoint] [21,22]. Furthermore, it shall be scrutinized to what extent the choice of treatment depends on anatomic and physiologic damage severity.

## Methods/Design

### Trial design

This trial is designed as a randomized controlled two-arm interventional multicenter trial. No blinding is performed. Both damage control and primary definitive surgery are standard care.

### Objectives

Primary objective of the trial is to clarify the question of whether a risk adapted procedure in treating femoral shaft fractures in multiple trauma patients as opposed to an early definitive treatment strategy leads to an improved outcome with respect to morbidity and mortality and if yes at what costs.

Furthermore, it shall be scrutinized to what extent the choice of treatment depends on anatomic and physiologic damage severity.

### Eligibility

#### Inclusion criteria

• Multiple trauma (injury of at least two body regions)

• Injury severity score (ISS) ≥ 16

• Femoral shaft fracture which can be treated in principle by nail or fixateur externe

• Beginning of surgical treatment within 24 hours after trauma

• Patient aged 18 years and older

• Calculated probability of death between 20% and 60% [23,24]

• All factors known which are needed for the calculation of probability of death [age, ISS, Glasgow Coma Scale (GCS), base excess (BE), prothrombin time]

#### Exclusion criteria

• III° open fractures

• Endangerment of the patient by one of both strategies

• Refusal of one of both strategies by either the investigator or the patient

• Start of internal or external fracture fixation before randomization

• Participation in concurrent interventional trials

• Pregnancy

### Reasoning for inclusion and exclusion criteria

The inclusion of patients with multiple trauma and corresponding fractures arises from the question of the study itself. Patients with thoracic or cranial trauma will be included according to systematic review of literature.

As patients might be randomized into the group "primary definitive surgery", patients in whom this procedure is not feasible or can not be performed (begin of surgery not within 24 hours possible or different procedure initiated) must be excluded.

The calculation of the probability of death with the given formula (see below) is a validated method of estimating the probability of death in multiple trauma patients [23-25]. It is essential though that all parameters entered are present at the time of calculation. Patients with missing values that are needed can not be included into the study.

Considering probability of death at randomization will allow an equal distribution of global prognosis in both treatment arms. Because the most important factors that determine prognosis in multiple trauma patients are considered, a comparison of this heterogenic patient collective is possible.

Open fractures are not an exclusion criteria per se [26]. Only III° open fractures will be excluded from this study as many surgeons do not favour the option of nailing in such severe open fractures [27,28].

Patients included in or about to be included in other interventional trials or trials involving drugs of any kind must be excluded out of judicial and scientific reasons.

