### Method of assigning patients to treatment groups

All multiple trauma patients with femur shaft fractures and age > or = 18 years that present to the involved hospitals will be recorded and eligibility will be checked. The probability of death will be calculated on the trial website using clinical data as described below. If all inclusion criteria are fulfilled the patient will be randomized and documentation will be started (figure 1). Reasons for non-inclusions must be recorded. Allocation concealment will be guaranteed by internet randomization where patients have to be named before allocation to one of the therapy arms. The validated system for internet randomization will be provided by the Coordinating Center for Clinical Studies Cologne (KKSK). This system generates the allocation sequence as follows: The randomisation sequence is blocked using varying block sizes between 6 and 10. Furthermore, randomisation is stratified by study center, in order to adjust for center-specific variation in treatment routines.

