### Calculation of probability of death

The probability of death will be calculated according to the following formula of Rixen et al. [23,24]:

With:

BE - Base Excess (mmol/l)

Quick - Prothrombin time (%)

Age - Age of patient

GCS - Glasgow Coma Scale

ISS - Injury Severity Score

This calculation can be done by entering the five variables at the trial website just before randomization. The individual probability of death is visible to the investigator.

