### Statistical analyses

The main outcome variable is the maximum SOFA score during ICU stay. In order to have comparable periods, the time period for SOFA score assessment is limited to the first 28 days after trauma. Documentation of daily SOFA scores is continued in intermediate care or other high dependency units.

The maximum SOFA score will be compared using non-parametric statistics (U-test) due to the substantial skewness of the distribution. Since severity of trauma is assumed to be a major determinant of outcome (including rate of organ failure) the comparability regarding Injury Severity Score (ISS) is tested before analysis. In case of substantial imbalance (p < 0.15; U-test) a stratified analysis of outcome will be performed (two groups; ISS ≤/> 30 points).

Analysis will be done according to intention to treat; regarding to the per protocol (PP) analysis we expect the PP-population to be 5% less.

There will be one interim analysis of data collection when about half of the expected sample size has been included (70 cases). The p-value for the interim analysis will be set at 0.005 so that the final analysis will be done at a significance level of 0.048, according to Fleming and O'Brien [31].

During interim and final analysis, a detailed safety analysis will be performed by comparing predicted and observed survival within each group and reviewing individual cases of non-survivors.

In addition, all secondary endpoints mentioned in the protocol will be considered for explorative analysis, because these factors are repeatedly named in the discussion about the advantages of damage control orthopedics. The aim of presenting all these data is not a confirmative statistical testing, but rather to serve as a basis for comparative analyses in future meta-analyses regarding damage control orthopedics versus early total care strategies.

The hospital perspective on costs includes the initial and all secondary operations or readmissions until one year after randomization. As most costs during hospital stay are caused by surgery itself and ICU care, data collection and statistical analysis will focus on these two aspects. The results will be reported as a cost-effectiveness analysis using life-years lost as the measure of treatment benefit. These analyses will employ decision-analytic models for the optimum management of multiply injured patients with femoral shaft fracture.

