Although mortality would have been the most appreciated endpoint, a trial with mortality as the main endpoint would need approximately 1300 patients per arm. In addition to the fact that such a trial is almost undoable for practical reasons the concentration on mortality does not cover all aspects of the planned intervention since the damage control approach primarily tries to limit the sequelae of the "second hit" by surgical intervention. This is reflected by the measurement of organ failure by appointing maximum values for patients who died. The SOFA score has been developed for the sequential evaluation and description of organ failure and has been shown to be a suitable indicator of prognosis in trauma patients [29].

A significant effect may only be shown in a group of medium probability of death (20-60%), especially concerning maximum SOFA-score, as the type of procedure chosen in patient groups of very high or very low mortality will most likely have only a minimal effect on this endpoint.

Because the most important factors that determine prognosis in multiple trauma patients are considered, a comparison of this heterogenic patient collective is possible.

In the current literature, another facet of the optimal surgical treatment in multiple trauma patients is discussed: Biochemical/immunologic factors. It has been shown that the traumatic tissue damage stimulates a maximal activation of the immune system, which leads to its depletion and debilitation [34-36]. As a consequence of a failing immune system a systemic inflammatory response syndrome (SIRS) or sepsis can occur. Both are potentially life threatening complications, in the course of which all organ systems can be affected [34,37,38].

Some of the best analyzed pro-inflammatory cytokines are tumor necrosis factor (TNF)-α [39,40], and the interleukines (IL)-6 and IL-8 [41-43]. Circulating IL-6 is quickly detectable after trauma [42] and has been shown to correlate with trauma load [44].

But so far, the transfer of results into clinical context and the verification for potential decision making (therapy) with respect to risk reduction during secondary surgical procedures after trauma failed.

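### The calculated probability of death limits who enters the trial but does not balance the arms, so the claimed equal prognosis is not secured beyond chance

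*Protocol article*

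**What the plan says.** Under Reasoning for inclusion and exclusion criteria, the protocol article says: "Considering probability of death at randomization will allow an equal distribution of global prognosis in both treatment arms". The conclusion drawn there is repeated in the Discussion: "Because the most important factors that determine prognosis in multiple trauma patients are considered, a comparison of this heterogenic patient collective is possible".

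The other sections describe what is done with the score:

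- **Eligibility.** Patients enter only if the score lies between 20% and 60% and all five inputs (age, ISS, GCS, base excess, prothrombin time) are known.
- **Timing.** Calculation of probability of death says: "This calculation can be done by entering the five variables at the trial website just before randomization".
- **Allocation.** Method of assigning patients to treatment groups says: "The randomisation sequence is blocked using varying block sizes between 6 and 10", and then: "Furthermore, randomisation is stratified by study center, in order to adjust for center-specific variation in treatment routines". No other allocation factor is named.
- **Primary analysis.** Statistical analyses says: "The maximum SOFA score will be compared using non-parametric statistics (U-test) due to the substantial skewness of the distribution". ISS is first compared between the arms. If p < 0.15, outcome is analysed in two ISS strata, cut at 30 points.
- **Other uses of prognosis.** Predicted and observed survival are compared within each arm in the safety analysis. Other baseline characteristics reserves the RISC score for explorative adjustment.

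**The concern.** An entry window narrows the range of risk among randomised patients. It does not distribute that risk between the arms. For that, the score would have to enter the allocation or the analysis, and the sections describing these do not use it. The reasoning section thus credits the design with a mechanism that the design does not contain.

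The score is closely tied to the endpoint. A patient who dies within 28 days is given 20 SOFA points, and the eligible range of predicted death is threefold. If the arms differ by chance on predicted death, a reader of the results will ask whether the difference in maximum SOFA reflects treatment or case mix. The primary analysis answers only through ISS, and only if a significance test on baseline data happens to trigger it.

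**Working it through.** **1. The plan's own sample size.** Inputs from Proposed sample size/Power calculations: standardised effect 0.5, alpha 0.05 (taken as two-sided), power 0.80.

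- Normal approximation: n = 2 × (1.960 + 0.842)² / 0.5² = 62.8, so 63 per group. The t-test calculation gives 63.8, so 64, as stated.
- 64 × 1.10 = 70.4, so about 70 per group and 140 in total. The figure reproduces.

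**2. Balance when allocation ignores the score.** The standard error of a standardised mean difference is sqrt(2/70) = 0.169, whatever the SD of the score.

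- 95% range: 1.96 × 0.169 = ±0.33.
- Chance of exceeding 0.2 in either direction: 0.2 / 0.169 = 1.18, two-sided probability 0.237, about 24%.
- A simulation of 140 patients in 15 equal-sized centres, with blocks of 6, 8 and 10 within centre (6,000 runs), gives 23% to 24% and a mean difference of zero. Stratifying by centre gives no protection on the score when the score is unrelated to centre, as simulated.

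**3. The same in percentage points.** The document gives no distribution for the score, so two are assumed.

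| Assumed distribution on 20–60% | SD (points) | SE of arm difference | 95% range |
|---|---|---|---|
| Uniform | 40/sqrt(12) = 11.5 | 11.55 × 0.169 = 1.95 | ±3.8 |
| Skewed to the low end, 20 + 40 × Beta(1,2) | 40 × sqrt(1/18) = 9.4 | 9.43 × 0.169 = 1.59 | ±3.1 |

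**4. Translation to SOFA points (illustrative).** Assume predicted risk equals actual 28-day risk and survivors average 6 points, so a death adds 14. The uniform case gives 0.038 × 14 = ±0.54 points and the skewed case 0.031 × 14 = ±0.43. For gaps of 10 to 16.7 points, the uniform range runs from ±0.38 to ±0.64. The upper gap is 20 minus the trauma-admission mean of 3.3 in the sample-size section.

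**5. How much of the noise this is.** On the same assumptions, with 40% deaths, the outcome SD from deaths alone is 14 × sqrt(0.4 × 0.6) = 6.9. The 95% chance range of the arm difference is then 1.96 × 6.86 × 0.169 = ±2.3 points.

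- Share due to the score: (0.54 / 2.27)² = 5.6%. The gap cancels, since the share equals var(p) / [mean(p) × (1 − mean(p))] = 0.0133 / 0.24.
- Skewed case (mean risk 33.3%): 0.00889 / 0.222 = 4.0%.

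This counts only the route through deaths. Spread among survivors would lower the share. Any relation between the score and survivors' SOFA would raise it.

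**6. The ISS safeguard.** Under sound randomisation, a baseline test at p < 0.15 triggers in about 15% of trials by chance. In the rest the primary test is unstratified. Even when triggered, the split leaves out age, GCS, base excess and prothrombin time.

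**The case against.** The strongest reply is that randomisation balances prognosis in expectation, that the window caps the absolute size of any chance imbalance, and that chance imbalance is already covered by the type I error of the test. All of this stands. A reader might infer that the arms will be unbalanced, or that the comparison is biased. The documents support neither.

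A reader might also infer that the score plays no part in design or analysis. It does: it defines the population and enters the safety analysis within each arm. Severity is not ignored either, because the ISS rule exists and RISC adjustment is planned as exploration. Nor can the score be called the best available predictor. The article does not rank predictors, and it credits RISC with very good prognostic capacity.

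The ±0.5 SOFA points could be read as an error of one third of the 1.5-point target. That reading fails. The figure is the edge of a 95% range, it rests on assumed inputs, it describes means while the test uses ranks, and it is a small part of chance variation already present.

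Stratifying by centre alone is defensible with about 9 patients per centre (140 / 15). Supplementary adjusted analyses may also stand in an analysis plan that is not shown. Neither point removes the conflict: the article states the allocation method and the primary test outright, and they do not do what the reasoning section says.

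**Conclusion.** The point holds as an inconsistency between the stated rationale and the stated methods, together with a missed, inexpensive improvement to the primary analysis. Equal prognosis is not ensured by considering the score. It rests on randomisation, with about a 24% chance of a standardised difference above 0.2 at 70 per arm. That figure depends only on the arm size.

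The consequences are limited. No fault in the allocation, the validity of the test or the sample size follows. The loss of precision is modest, 4.0% to 5.6% of variance under the two assumed risk distributions, with predicted risk taken as calibrated to 28-day death. The larger cost is credibility: the plan promises a comparability that it does not secure, and its one safeguard is conditional and covers one of five components.

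**What to change.** 1. **Primary analysis.** Drop the ISS pretest and its conditional split. Prespecify an adjustment for the calculated probability of death that applies whatever the baseline data show. The U-test takes no covariate, so the method must be named. One option is a van Elteren test stratified at 20–40% and 40–60%, which is the stratified form of the planned test. Another is a rank-based or proportional-odds model with the continuous score. Use the same method at the interim and the final analysis, and fix it before the interim data are examined.
2. **Wording.** In the reasoning section and the Discussion, say that the score restricts eligibility and that balance between arms relies on randomisation.

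**Cost.** The stated primary test changes, which needs an amendment and not just an edit of the text. The sample size stays at 140. No patient is lost to missing covariates, because eligibility requires all five inputs.

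**Optional and not needed: the score in the allocation.** Crossing two score levels with 15 centres gives 30 strata of about 4.7 patients (140 / 30), below the smallest block of 6. In the simulation this lowers the chance of a standardised difference above 0.2 only to about 11%. Minimisation avoids thin strata, but the trial is open-label and the investigator sees the score, so assignments could become easier to predict.
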